### Study endpoints

The primary study endpoints will be the rate of eGFR decline and the incidence of ESRD.

The secondary endpoints will include measures of conventional and geriatric outcome measures, such as: rate of CKD complications (anemia, hyperphosphatemia, acidosis, hypoalbuminemia, hyperparathyroidism, hyperkaliemia); rate of major comorbidities (e.g. hypertension and CV diseases) [43]; overall and CV mortality; adverse drug reactions (ADRs); self-reported disability and objectively measured physical performance decline [39, 40, 48]; cognitive impairment [41]; depression [42]; malnutrition/undernutrition [46, 47]; health-related quality of life [52]; healthcare resource consumption, including the estimation of caregiver burden [53].

Informations on vital status during follow-up will be obtained by interviewing the patients and/or their formal and/or informal caregivers. For mortality during the follow-up period, date, place and cause of death will be retrieved by certificates of death exhibited by relatives or caregivers.

### Data management and statistics

The SCOPE project will enroll a total of 2450 participants. On the basis of the primary end-points, a sample of 1900 patients will be able to differentiate between two equally sized subgroups according to a standardized difference in yearly rate of GFR decline of 0.13 mL/min/1.73m^2^ with a power of 80%. The same sample size allows to detect a hazard ratio of 1.2 in time-to-event analyses with 80% power for incidence of ESRD. Thus, even a 20% drop out rate will not affect statistical power of the study.

Every effort will be made to collect all data at the specified time points. In the case of missing (and not recoverable) data on primary endpoints, we will make the assumption that data are missing completely at random. Analyses will be carried out applying the list-wise deletion of cases with missing values in order to obtain unbiased estimations. Multiple imputation of missing data will be applied only for secondary endpoints and co-variates when found appropriate.

For continuous outcomes, generalized mixed models will be used while for dichotomous outcomes, random effect logistic or Cox regression will be applied. Effect modification by age and gender will be investigated using multiplicative interaction analyses.

Relevant exposure and co-variates will be selected based on plausible underlying hypothesis. Directed acyclic graphs may be used in order to create parsimonious multivariable models with minimized confounding. If appropriate, repeated measurements of exposure and co-variates will be included in the models.

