### Study population

Persons aged 75 years and older, visiting the outpatient clinics of participating institutions are eligible for inclusion. The study design aims at minimizing self-selection bias and enrolling real-world patients without stringent inclusion/exclusion criteria. The few exclusion criteria are outlined in Table 1. Therefore, no other inclusion criteria will be considered. The SCOPE study aims to finally enroll 2450 participants.

**Table 1 Tab1:** Exclusion criteria for participants enrollment into the SCOPE project

• Age < 75 years	
• End stage renal disease (< 15 mL/min/1.73 m2) or dialysis at time of enrollment	
• History of solid organ or bone marrow transplantation	
• Active malignancy within 24 months prior to screening or metastatic cancer	
• Life expectancy less than 6 months	
• Severe cognitive impairment (Mini Mental State Examination < 10)	
• Any medical or other reason (e.g. known or suspected inability of the patient to comply with the protocol procedure) in the judgement of the investigators, that the patient is unsuitable for the study	
• Unwilling to provide consent and those who cannot be followed-up	

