### Measured glomerular filtration rate

The assessment of measured glomerular filtration rate (mGFR) will be performed by single-dose inulin clearance [62, 63]. Participants will be asked to sign a separate informed consent to participate in this sub-study, while those not giving their consent will be retained in the main cohort study. The objective of this sub-study will be the derivation of new eGFR equation(s) based on already known and/or novel biomarkers. The accuracy of new equation(s) in predicting mGFR will represent the primary study endpoint. Accuracy will be assessed by P30 (percentage of estimates within 30% of the mGFR). A sample of 400 participants will enable us to detect a difference of 2% in P30 between the new equations (based on the innovative and novel biomarkers) and the BIS equations, with significance level 0.05 and power 0.8 (considering a 1-sample and 1-sided test). In addition, we have evaluated that the sample will be sufficient to detect a statistically significant difference in 4,3 points in the Area under the ROC curve using the new equation(s) for discriminating participants below the critical threshold of 60 ml/min/1.73 m^2^. Finally, the availability of mGFR in a subgroup of participants enrolled in the study will be used to investigate the relationship between innovative biomarkers and objectively measured kidney function.

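### The stated 80% power for a hazard ratio of 1.2 on incident ESRD gives no event rate, and with two equal groups it would need about half of the 1900 participants to reach ESRD within 24 months

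*Protocol article*

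**What the plan says.** The section *Study endpoints* makes ESRD a co-primary outcome: "The primary study endpoints will be the rate of eGFR decline and the incidence of ESRD". The section *Data management and statistics* first gives the basis for the slope endpoint: "a sample of 1900 patients will be able to differentiate between two equally sized subgroups", for a "standardized difference in yearly rate of GFR decline of 0.13 mL/min/1.73m^2^ with a power of 80" percent. The next sentence extends that number to the second primary endpoint: "The same sample size allows to detect a hazard ratio of 1.2 in time-to-event analyses with 80% power for incidence of ESRD". It gives no ESRD incidence, number of events, alpha, sidedness or exposure. The section then concludes that a 20% dropout leaves the study's power intact, without separating the two endpoints.

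The other relevant facts are these:

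- *Study population*: eligibility is age 75 or over and attendance at an outpatient clinic, with no CKD requirement. Table 1 excludes "End stage renal disease (< 15 mL/min/1.73 m2) or dialysis at time of enrollment".
- *Laboratory parameters and biomarkers*: an ESRD event is a GFR below 15 mL/min/1.73 m² or dialysis.
- *Study design*: follow-up is 24 months, with face-to-face visits at 12 and 24 months.

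**The concern.** A number of patients does not fix the power of a Cox or log-rank comparison; the number of events does. A hazard ratio of 1.2 is a small effect and needs many events. The power figure is printed for a primary endpoint without the one quantity that determines it, in a cohort where ESRD is excluded at entry and follow-up is short.

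If the figure is wrong, readers are told that the study can detect modest associations with ESRD when it may not be able to. A null ESRD result could then be taken as evidence against such associations. The dropout statement rests on the same sentence, so it carries the same reassurance.

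**Working it through.** **Inputs from the article.** Hazard ratio 1.2; power 80%; 1900 patients; 2450 enrolled; 24 months of follow-up.

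**Inputs assumed.**
- Group split: equal, carried over from the preceding sentence ("two equally sized subgroups"). The hazard-ratio sentence names no exposure.
- Alpha: not stated for the main cohort. The only one in the article belongs to the measured-GFR sub-study ("with significance level 0.05 and power 0.8 (considering a 1-sample and 1-sided test").
- ESRD incidence: not stated, so a range is used.

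**Step 1. Reproduce the slope calculation, to infer the alpha convention.** Total n = 4(z_α + z_β)²/d², with d = 0.13 and z_β = 0.842.
- Two-sided 0.05: 4 × (1.960 + 0.842)²/0.13² = 4 × 7.849/0.0169 ≈ 1858 (929 per group). This is close to 1900; with 950 per group, power is 80.9%.
- One-sided 0.05: 4 × (1.645 + 0.842)²/0.0169 ≈ 1464.

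Two-sided 0.05 therefore appears to be the convention used, and the slope half of the justification holds.

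**Step 2. Events needed for a hazard ratio of 1.2 at 80% power.** ln(1.2) = 0.1823; squared, 0.03324.

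| Reading | Formula | Events | Share of 1900 |
|---|---|---|---|
| Two equal groups, two-sided 0.05 (Schoenfeld) | 4 × 7.849/0.03324 | 945 | 49.7% |
| Same, Freedman formula | | 950 | 50.0% |
| Two equal groups, one-sided 0.05 (Schoenfeld) | 4 × 6.183/0.03324 | 744 | 39.2% |
| Per SD of a continuous marker, two-sided 0.05 | 7.849/0.03324 | 236 | 12.4% |
| Per SD, one-sided 0.05 | 6.183/0.03324 | 186 | 9.8% |

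With all 2450 enrolled participants as the denominator, 945 events is still 38.6%.

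**Step 3. Power and detectable hazard ratio over an assumed range of two-year incidence (1900 patients, two-sided 0.05).** With D events:
- two-group power = Φ(0.1823√D/2 − 1.960) + Φ(−0.1823√D/2 − 1.960);
- per-SD power = Φ(0.1823√D − 1.960), where the opposite tail adds less than half a percentage point in this range;
- two-group hazard ratio detectable with 80% power = exp(2 × 2.802/√D).

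| Assumed incidence | Events | Two-group power at HR 1.2 | Per-SD power at HR 1.2 | Two-group HR detectable at 80% |
|---|---|---|---|---|
| 1% | 19 | 7% | 12% | 3.6 |
| 2% | 38 | 9% | 20% | 2.5 |
| 5% | 95 | 14% | 43% | 1.8 |
| 10% | 190 | 24% | 71% | 1.5 |
| 20% | 380 | 43% | 94% | 1.3 |

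The two-group figures count rejections in both directions. At 1% incidence, about 0.9 of the 7 points lie in the wrong direction.

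**Step 4. Dropout.** 2450 × 0.8 = 1960, which exceeds 1900. The arithmetic is sound for the slope endpoint, but it says nothing about the number of ESRD events.

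**The case against.** The strongest reply is that the check supplies inputs the article does not give. The sentence on ESRD states no alpha and no exposure, and the equal split belongs to the slope sentence. If the hazard ratio is meant per standard deviation of a biomarker, the need falls to about 236 events, and power at 5% or 10% incidence is 43% or 71%. The case mix may also be enriched: the Discussion describes the centres as experienced with patients at risk of renal impairment. And the slope endpoint justifies 1900 by itself, so the ESRD claim need not have driven enrolment.

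Much of this stands. The alpha, the split and the incidence are assumptions and are labelled so above, and the slope justification is not in question. But the per-SD reading is not stated, and it still needs about 12% incidence for 80% power. Enrichment would not plausibly bring a cohort with no CKD entry criterion to 39–50%. Nor is this detail left out because an article is condensed: the article prints the 80% without condition.

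Two stronger readings are tempting, and neither is supported.
- A reader might infer that the authors counted nearly every patient as an event. With 1900 events, power would be 97.8%. The printed 80% matches an event fraction of about one half, and the article does not show how it arose.
- A reader might infer that the ESRD analysis has almost no power, or that the claim is impossible. The article gives no incidence. Over 1–10%, two-group power runs from 7% to 24%, so the first description fits only the low end. *Not credible* is as far as the design facts go on the second.

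**Conclusion.** The power statement for ESRD is unsupported as written. On the two-group readings it holds only if about 744 to 945 of 1900 participants (39–50%) reach a GFR below 15 or dialysis within 24 months, which is not credible for this population. On the per-SD reading, which the article does not state, it holds only at about 12% incidence.

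The event counts rest on the assumed exposure form and alpha; two-sided 0.05 is inferred from the slope calculation. How far power falls below 80% depends on an incidence that the article does not give. The slope endpoint and its sample size are unaffected. Because the statement concerns a named primary endpoint and is cheap to correct, it should be corrected.

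**What to change.** - Withdraw the statement of 80% power for a hazard ratio of 1.2 on ESRD.
- Replace it with the assumed range of two-year ESRD incidence, alpha, sidedness, exposure form (two groups or per SD), expected events, and the hazard ratio that each number of events detects with 80% power. With two equal groups and two-sided 0.05, for example, 19, 38, 95 and 190 events detect about 3.6, 2.5, 1.8 and 1.5.
- State that the 1900 is justified by the GFR-decline endpoint, and limit the 20% dropout statement to that endpoint.
- Report ESRD associations with confidence intervals, so that a null result is not read as excluding modest effects.

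The cost is a wording change, with no extra patients, visits or data; if handled as an amendment, it needs the Scientific Advisory Board's approval. The stated power for ESRD will look much less favourable. Whether ESRD should remain a primary endpoint, or be combined with other renal events, is a separate design choice that this point does not settle.

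### The primary eGFR slope is to be analysed by list-wise deletion under a missing-completely-at-random assumption that the protocol's own description of the cohort does not support; the mean slope can be biased, and the planned mixed model makes the deletion unnecessary

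*Protocol article*

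**What the plan says.** All from the Protocol article.

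- Study endpoints: "The primary study endpoints will be the rate of eGFR decline and the incidence of ESRD".
- Data management and statistics, on missing primary-endpoint data: "we will make the assumption that data are missing completely at random". The next sentence gives the handling: "Analyses will be carried out applying the list-wise deletion of cases with missing values in order to obtain unbiased estimations".
- Same section: "Multiple imputation of missing data will be applied only for secondary endpoints and co-variates when found appropriate".
- Same section, on the model: "For continuous outcomes, generalized mixed models will be used". Logistic or Cox regression is named for dichotomous outcomes.
- Study visits and Telephone follow-up: blood for creatinine is taken at enrolment and at the 12- and 24-month face-to-face visits. The 6- and 18-month contacts are telephone interviews.

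**The concern.** MCAR means that whether an eGFR value is missing has nothing to do with the participant's kidney function or health. The protocol describes a cohort in which that is unlikely:

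- Background links CKD to morbidity and mortality, and to frailty, disability and cognitive impairment.
- Table 1 (Study population) excludes people expected to live less than 6 months, while follow-up lasts 24 months.
- Discussion expects multimorbidity in many participants.
- Study endpoints lists death, disability and cognitive impairment among the outcomes.

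Someone too ill to attend a visit has no eGFR for it, and someone who dies before month 24 has no 24-month value. List-wise deletion then also removes the baseline and 12-month values of those people, and the slope is estimated only in those who completed every visit.

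The plan also works against itself. A likelihood-based mixed model uses incomplete series and is valid under MAR, where missingness may depend on values already observed. Deleting incomplete cases first gives up that advantage. Because imputation is confined to secondary endpoints and covariates, a primary endpoint gets the weakest handling in the plan. At stake is the estimated rate of eGFR decline in this population.

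**Working it through.** **1. The plan's own sample size.** "The SCOPE project will enroll a total of 2450 participants", and "a sample of 1900 patients will be able to differentiate between two equally sized subgroups" at a standardized difference of 0.13 with 80% power. The section gives no significance level for this calculation; 5% two-sided is assumed.

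n per group = 2(1.960 + 0.842)² / 0.13² ≈ 929, so 1858 in total, within 3% of 1900. Power with 950 per group is 0.81. After 20% dropout, 2450 × 0.8 = 1960 remain, above 1900. The figure reproduces, and the loss of numbers is allowed for. What remains is selective loss.

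**2. Simulation A: mean slope.** Every input is an assumption, because the documents give none: baseline SD 14, mean slope −1.50 mL/min/1.73 m² per year, slope SD 2.5, residual SD 4, visits at 0, 1 and 2 years, 20% missing at 24 months, N = 400,000.

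Missingness: logit P(missing) = a − ln(OR) × z, where z is the standardised driver and a is set to give 20% missing. OR is thus the odds ratio of being missing per SD lower value of the driver (for the two decline drivers, per SD faster decline).

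Estimator: a random intercept-and-slope model fitted by generalised least squares with the true variance components, once on completers only (list-wise) and once on all available visits.

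| Driver of missingness | Method | OR 1.25 | OR 1.5 | OR 2 | OR 3 |
|---|---|---|---|---|---|
| Observed 0–12 month change (MAR) | List-wise | −1.39 | −1.32 | −1.20 | −1.08 |
| | All visits | −1.50 | −1.50 | −1.50 | −1.50 |
| True slope (missing not at random, MNAR) | List-wise | −1.39 | −1.30 | −1.18 | −1.04 |
| | All visits | −1.44 | −1.39 | −1.32 | −1.23 |
| Low baseline eGFR only (MAR) | List-wise | −1.52 | −1.54 | −1.57 | −1.61 |
| | All visits | −1.50 | −1.50 | −1.50 | −1.50 |

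At OR 1 (MCAR) both methods give −1.49 to −1.50.

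In the first row decline is understated by (1.50 − 1.39)/1.50 ≈ 7%, then 12%, 20% and 28%. In the low-baseline row it is overstated by about 1% to 7%.

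**3. Simulation B: a second set of assumed inputs.** Slope SD 2, error SD 4, 24% missing at 24 months, reference slope −1.0, true group difference −0.50, N = 400,000. Dropout depends on the observed 12-month change with log-odds 0.05, 0.08 or 0.12 per mL/min.

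- Same dependence in both groups: list-wise mean slope in the reference group is −0.85 to −0.68 against −1.0, an understatement of 15% to 32%. The group difference is nearly unchanged: −0.52, −0.48 and −0.48 list-wise, against −0.52, −0.48 and −0.49 with all visits.
- Dependence 0.3 times as strong in one group: the list-wise group difference falls to −0.40, −0.34 and −0.25.
- Same 0.3 ratio, but dropout driven by the true slope: −0.46, −0.43 and −0.40 list-wise, against −0.47, −0.45 and −0.44 with all visits.

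**4. Group contrast in simulation A.** With one common mechanism and a true difference of −0.325 (0.13 × 2.5), the list-wise estimate changes little at OR up to 1.5. At OR 3 with missingness driven by the true slope it is −0.28, against −0.30 with all visits. Simulation error for this contrast is about √(2.5² + 4²/2) × √(4/400,000) ≈ 0.012.

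**The case against.** **The sentence is correct under its own premise.** The protocol states MCAR first, and under MCAR list-wise deletion is unbiased. This stands as logic. The fault lies in resting a primary endpoint on MCAR in this cohort.

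**Cases might mean visit records.** If only the missing visit is dropped, the mixed model still uses the other visits. The wording does not say so, and pairing deletion with MCAR points to removal of participants. If visit records were meant, MCAR is not needed and the text should be corrected all the same.

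**Stronger readings that a reader might infer, and that the documents do not support:**

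- *Differences between frail and robust, or high- and low-biomarker, groups are necessarily attenuated.* In the simulations this happens to a material degree mainly when dropout depends on decline more strongly in one group. Nothing in the documents supports a particular ratio such as 0.3. This matters because the sample size is built on a contrast between subgroups.
- *Slopes are certain to be too shallow.* Dropout driven only by low baseline eGFR biases the slope slightly the other way.
- *The mixed model cures the problem.* It does so under MAR. If missingness follows the true slope, it reduces the bias in the mean slope without removing it, and does little for the group contrast.
- *The dropout allowance is wrong.* The protocol says "Thus, even a 20% drop out rate will not affect statistical power of the study". As a statement about numbers it holds: 1960 remain, above 1900.
- *The same bias applies to ESRD.* Cox regression can censor incomplete follow-up, and death before ESRD is a competing event rather than a missing value. No ESRD analysis was run, so the slope figures do not carry over.
- *The lack of an MNAR analysis is a defect.* That commonly belongs to the statistical analysis plan, which is not shown.

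**Conclusion.** The point holds for the eGFR slope. The protocol fixes a rule that is valid for the mean slope only under an assumption its own text makes implausible, and it does so where its planned model needs only a weaker one. In every scenario tested other than MCAR, the mixed model on all visits came closer to the true mean slope than list-wise deletion.

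The size is conditional. With 20 to 24% missing at 24 months and dropout related to the observed 12-month change, mean decline is understated by roughly 7 to 30%. The missing fraction at 24 months, the variance components and the strength of the dropout relation are all assumptions, and only missing 24-month values were simulated. Confidence is high that MCAR with list-wise deletion is the wrong primary rule. Neither the direction nor the size of the bias in this study can be derived from the documents.

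**What to change.** Replace the MCAR and list-wise sentences with wording such as:

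> The primary eGFR slope is estimated by a likelihood-based linear mixed model with random intercept and slope, using every available eGFR value from all participants with at least one value, under a missing-at-random assumption and with baseline predictors of dropout in the model. A complete-case analysis is a sensitivity analysis only.

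Delete the statement that list-wise deletion gives unbiased estimates. An MNAR sensitivity analysis, such as a joint model of slope with death or dropout, or delta-adjusted multiple imputation, is advisable, because MAR may not hold where death and illness drive the loss.

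The cost is a change of wording in the protocol and analysis plan. No new data are needed, and the mixed model is already planned. The optional sensitivity analysis adds one model.

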### Economic monitoring

The economic analysis of the SCOPE project will include: i) cost of screening/diagnosis; ii) cost of follow-up (e.g. pharmacological treatment, specialist visits, laboratory visits over the 2-year follow-up); iii) cost of CKD complications (e.g. emergency room access, hospital admission, haemodialysis, etc.); iv) other health-related costs (e.g. hospital out-patient care referrals, nursing home placements, use of home care services). With this analysis, it will be possible to determine main predictors of costs in CKD using multivariate regression and to establish cost-effective ratio of the intervention (overall healthcare costs, divided by efficacy, expressed as survival or quality-adjusted survival).

In order to assess the cost-benefit profile of the screening program on a longer time horizon, clinical and economic results of the SCOPE project will be used to run a projection (10–15 years) using Markov modelling. The analysis consists in evaluating a hypothetical cohort of CKD patients, whose healthcare status is categorized into different initial Markov states, based on CKD biomarkers. Patients can move from one state to another, according to certain probabilities that will be derived from the SCOPE project, and can develop complications, such as cardiovascular morbidity, renal failure and need of dialysis, CKD related and non-related death.

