## Methods

### Study design

The SCOPE study is designed as an observational, multinational, multicenter, prospective cohort study in persons older than 75 years across Europe. This study is carried out in seven countries, including Austria, Germany, Israel, Italy, the Netherlands, Poland and Spain. Participants will undergo clinical and laboratory evaluations at the baseline (recruitment), and will be followed up at face to face visits at months 12 and 24 following enrollment. An intermediate telephone follow-up will be carried out at 6 and 18 months following recruitment. Figure 1 shows the schematic flow of the observational clinical study.

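### The cost-effectiveness ratio is defined as an average within one fully tested cohort, and the long-term model covers CKD patients only; neither matches the stated question about the screening programme

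*Protocol article*

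**What the plan says.** Economic monitoring in the protocol article sets out two analyses that bear on the value of screening.

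- **Within the study.** Four groups of costs are collected, the first being screening and diagnosis. From these the plan is "to establish cost-effective ratio of the intervention (overall healthcare costs, divided by efficacy, expressed as survival or quality-adjusted survival").
- **Projection over 10 to 15 years.** The purpose is given as "In order to assess the cost-benefit profile of the screening program on a longer time horizon". The model is then described: "The analysis consists in evaluating a hypothetical cohort of CKD patients, whose healthcare status is categorized into different initial Markov states, based on CKD biomarkers". Moves between states happen "according to certain probabilities that will be derived from the SCOPE project".

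Other sections fix the setting:

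- Study design: "The SCOPE study is designed as an observational, multinational, multicenter, prospective cohort study in persons older than 75 years across Europe".
- Study population: "Persons aged 75 years and older, visiting the outpatient clinics of participating institutions are eligible for inclusion". CKD is not required for entry.
- Study visits: creatinine, urinary albumin and the albumin-to-creatinine ratio (ACR) are measured in participants at enrolment and at both face-to-face follow-up visits.
- Table 3, footnotes: results of the current tests are available at once; alternative and innovative markers stay hidden until the analysis.
- Background: better screening accuracy should limit underdiagnosis and also the risk and cost of overdiagnosis.

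**The concern.** A cost-effectiveness statement about screening needs a contrast: the extra cost of one strategy over another, divided by the extra health. The formula in the article has no difference term, and the cohort has no unscreened or differently screened group to supply one. The quotient therefore describes what it costs to care for this cohort per unit of survival. Calling it the cost-effectiveness of an intervention invites readers to take it as evidence on screening.

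The second mismatch is between the model's purpose and its population. A screening programme tests everyone eligible, and a large part of its cost and harm falls on people who do not have the disease. A projection that follows CKD patients has no place for them, although the Background section names overdiagnosis as something to be weighed.

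The Discussion expects the economic results to inform care planners and public health, and links the project to European recommendations on screening. A misread ratio could therefore travel beyond this study.

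**Working it through.** The article states no figure for the economic analysis, so there is nothing to reproduce. The check compares the stated formula and model population with the stated question. **All cost, QALY and prevalence values below are assumptions; none comes from the article.**

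**1. What the planned ratio measures**

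Planned ratio = C/Q, with C the total cost and Q the survival or QALYs in the cohort.

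Incremental ratio = (C1 − C0)/(Q1 − Q0), with 1 for screening and 0 for the reference strategy.

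Take C1 = 20,000 and Q1 = 1.4 QALYs per person over two years. The planned ratio is 20,000/1.4 = 14,286. Now vary what screening adds:

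| Added cost | Added QALYs | Planned ratio | Incremental ratio |
|---|---|---|---|
| 100 | 0.001 | 14,286 | 100,000 |
| 100 | 0.005 | 14,286 | 20,000 |
| 100 | 0.01 | 14,286 | 10,000 |
| 100 | 0.05 | 14,286 | 2,000 |
| 500 | 0.001 | 14,286 | 500,000 |
| 500 | 0.005 | 14,286 | 100,000 |
| 500 | 0.01 | 14,286 | 50,000 |
| 500 | 0.05 | 14,286 | 10,000 |

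Even if the average ratio without screening were known, it would barely move. It would be (20,000 − 500)/(1.4 − 0.001) = 13,939 in the worst of these cases and (20,000 − 100)/(1.4 − 0.05) = 14,741 in the best.

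A second example has no health gain at all. With 8,000 per year and 0.70 QALY, the ratio is 8,000/0.70 = 11,429. Adding a test at 50 gives 8,050/0.70 = 11,500, a rise of 0.6%, although money is spent for nothing.

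**2. Whether the cohort supplies the missing contrast**

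The plan gives everyone the current tests, so outcomes without them are not observed. The newer markers are hidden until the analysis, so they cannot alter care or outcomes during follow-up. The Discussion says that care is tailored individually at each centre. Transition probabilities taken from this cohort thus describe one regime: current testing followed by usual care.

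**3. Who is outside the Markov cohort**

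People tested per CKD case = 1/p, and participants without CKD = 2450 × (1 − p), where p is the prevalence and 2450 the planned enrolment.

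| Assumed p | Tested per case | Without CKD, of 2450 |
|---|---|---|
| 10% | 10 | 2205 |
| 20% | 5 | 1960 |
| 30% | 3.3 | 1715 |
| 50% | 2 | 1225 |

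If testing were charged to cases only (the article does not say how it is charged), the omitted testing cost per case at 50 per test would be 50 × (1/p − 1). That is 50 at 50% prevalence and 117 at 30%, or 0.6% and 1.5% of an assumed annual cost of 8,000. This is small against total cost. The proper yardstick, however, is the incremental cost of screening, to which testing contributes directly. The consequences of false positives come on top and cannot be sized from the article.

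**The case against.** The strongest reply is that this is a short summary in a journal article. Named strategies, a comparator, external inputs and sensitivity analyses may stand in a full protocol or health-economic plan, and their absence here is no error. That is accepted. The point rests only on what the article does state: the formula of the ratio and the population of the model.

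The economic work also has aims that remain sound, namely describing costs arising from CKD and finding their predictors. It is not among the primary or listed secondary endpoints. Both statements stand.

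Several stronger readings are tempting but not supported:

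- *The intervention does not exist.* The authors may well mean the screening programme, whose cost is the first item on their list. What can be said is that the cohort offers no contrast for its effect.
- *The ratio will make screening look favourable.* It is uninformative, not biased in one direction. In the zero-gain example above, it becomes slightly worse.
- *Missed cases cannot be represented, or perfect case finding is assumed.* A missed case has CKD and can sit in a CKD cohort, and the article does not say that the modelled patients have already been detected. Only true negatives and false positives lie outside.
- *People without CKD are left out of the whole economic analysis.* The within-study costing does not exclude them. The restriction is stated for the Markov projection.
- *Costs per case are understated several-fold.* The multiples 1/p concern testing cost alone and depend on assumed prevalence and on how testing is charged.

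**Conclusion.** The point holds in this limited form. As written, the within-study ratio is an average and cannot show what screening adds: on the assumed inputs, one planned value of 14,286 per QALY is compatible with incremental ratios from 2,000 to 500,000. The denominator may be life-years instead of QALYs, which does not change the argument. The Markov projection, as described, follows CKD patients while its purpose concerns a programme applied to all outpatients aged 75 and over, subject to the exclusions in Table 1. It leaves out half to nine-tenths of those tested if prevalence is 50% to 10%.

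The mismatch in formula and population follows from the text alone; every size rests on assumed values. It should be corrected before the economic analysis is run, but it does not touch the primary endpoints, the data collection or the regression on predictors of CKD costs.

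**What to change.** - Replace the average ratio with incremental cost and incremental life-years or QALYs between named screening strategies, including a no-screening or current-practice reference. Report them as an incremental cost-effectiveness ratio or net monetary benefit.
- Start the Markov cohort from all outpatients aged 75 and over, with a no-CKD state, so that true negatives and false positives carry their costs and consequences.
- Take the accuracy of eGFR-based tests from the measured-GFR sub-study where it applies. It has 400 separately consenting participants and already examines discrimination at 60 ml/min/1.73 m². It cannot validate the ACR component.
- Take the effects of detection, and outcomes under the reference strategy, from external sources, and vary them in sensitivity analysis.
- If this is not done, present the within-cohort figure as a descriptive cost per life-year or QALY and drop the claim that it measures the cost-effectiveness of an intervention.

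The cost is additional modelling work and greater dependence on external assumptions. No new data collection is needed: quality of life (Euro-QoL 5D) and resource use are already recorded.
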